## Abstract

**Background:**

There is poor viral load monitoring (VLM) and inadequate management of virological failure in HIV-positive individuals on antiretroviral therapy in rural KwaZulu-Natal, South Africa. This could be contributing to increasing HIV drug resistance in the setting. This study aims to investigate the clinical and process impediments in VLM within the health system and to evaluate a quality improvement package (QIP) to address the identified gaps. The QIP comprises (i) a designated viral load champion responsible for administrative management and triaging of viral load results (ii) technological enhancement of the routine clinic-based Three Interlinked Electronic Register (TIER.Net) to facilitate daily automatic import of viral load results from the National Health Service Laboratory to TIER.Net (iii) development of a dashboard system to support VLM.

**Methods/design:**

The study will evaluate the effectiveness of the QIP compared to current care for improving VLM and virological suppression using an effectiveness implementation hybrid type 3 design. This will use a cluster-randomised design with the primary healthcare clinics as the unit of randomisation with ten clinics randomised in a 1:1 ratio to either the intervention or control arm. We will enrol 150 HIV-positive individuals who had been on ART for ≥ 12 months from each of the ten clinics (750 in 5 intervention clinics vs. 750 in 5 control clinics) and follow them up for a period of 12 months. The primary outcome is the proportion of all patients who have a viral load (VL) measurement and are virally suppressed (composite outcome) after 12 months of follow up. Secondary outcomes during follow up include proportion of all patients with at least one documented VL in TIER.Net, proportion with VL ≥ 50 copies/mL, proportion with VL ≥ 1000 copies/mL (virological failure) and subsequent switch to second-line ART.

**Discussion:**

We aim to provide evidence that a staff-centred quality improvement package, designated viral load monitoring champion, and augmentation of TIER.Net with a dashboard system will improve viral load monitoring and lead to improved virological suppression.

*Trial registration:* This trial is registered on ClinicalTrials.gov on 8 Oct 2021. Identifier: NCT05071573; https://clinicaltrials.gov/ct2/show/NCT05071573?term=NCT05071573&draw=2&rank=1

## Background

Antiretroviral therapy (ART) scale-up in sub-Saharan Africa (SSA) has been rapid with an estimated 16.4 million individuals on ART by the end of 2018 [1]. The increased expansion in the indication for ART use would result in earlier initiation of treatment and if adherence is suboptimal, could lead to virological failure and the likely development of drug resistance. The likelihood of transmission of resistant virus will depend on ART coverage, duration of ART roll-out and the proportion and absolute numbers of individuals with virological failure [2–4]. Conditions that would influence transmission of resistant virus include proportion of failures with resistant virus, time spent on failing regimen, viral load (VL) of patients with resistant virus, fitness of the resistant virus and the transmission probability compared with ART-naïve individuals [2]. The availability of viral load monitoring (VLM) in resource-rich countries, means individual failing treatment are identified early and switched to alternative suppressive ART. In contrast, many sub-Saharan African countries rely on World Health Organisation (WHO) immunological and clinical criteria for identifying treatment failure which has poor sensitivity and specificity [5]. In settings where there is availability of VLM, their effectiveness has been hampered by poor adherence to monitoring guidelines by healthcare providers [6].

South Africa has the biggest HIV treatment programme in the world with 7.7 million individuals living with HIV and 62% currently receiving ART within a stretched health system [1]. VLM has been part of the public ART programme since roll-out in 2004 and requires people living with HIV (PLHIV) initiating ART to have a VL measured at 6 months and 12 months after ART initiation and 12-monthly thereafter if virologically suppressed [7, 8]. Those with a VL ≥ 1000 HIV-1 RNA copies/mL should be retested after 3 months of adherence counselling support, and then either retained on first-line therapy if re-suppressed or switched to second-line therapy if VL ≥ 1000 copies/mL [7].

However, little is known about how these VL guidelines are being used in clinical decision-making in public ART programmes in SSA. In formative research utilising an electronic database, the Three Interlinked Electronic Register (TIER.Net) [9], of a programmatic ART cohort in rural KwaZulu-Natal, we observed infrequent VLM and sub-optimal management of virological failure. The study showed that only 34% of patients had a viral load documented after 12 months on ART. Only 20% of individuals in the cohort were confirmed to have virologic re-suppression or change to second line therapy after virologic failure, and those who changed therapy did so a median of one year after virologic failure [10]. With the expansion in the indications for ART use [11], such delays are likely to have significant deleterious individual and public health impacts through effects on patient morbidity, accumulation of drug resistance [12–14], and persistent risk of HIV transmission in the setting [15].

Findings from this formative research was presented in a series of workshops to healthcare providers, policy makers, researchers and community representatives using good participatory approaches with a view to co-produce health system interventions to address poor VLM. This protocol describes the proposed interventions and their evaluation. We hypothesise that a staff-centred quality improvement package (QIP) and technological augmentation of an existing electronic ART database (TIER.Net) would result in optimal VLM of patients on ART, prompt clinical management of virological failure and an overall improvement in virological suppression.

## Objectives

### Main trial objective

The main objective is to evaluate the impact of a combination of interventions that includes a staff-centred quality improvement package, designated viral load monitoring champion, and augmentation of TIER.Net with a dashboard system will improve viral load monitoring and lead to better virological suppression over a period of 12 months in comparison to the current standard of care.

### Secondary objectives

To identify health system specific gaps in VLM.To evaluate the cost and cost effectiveness of the intervention compared to standard careTo undertake a process evaluation assessing acceptability, fidelity, adaptation and contexts in the implementation of the intervention.

## Methods

### Trial setting

The trial will be hosted by the Africa Health Research Institute (AHRI), an independent scientific research institute and a Wellcome Trust Africa and Asia Programme. AHRI has two campuses 250 km apart; the Population Intervention Programme (PIP) study area in uMkhanyakude district in northern KZN with a population of 625,846, and a state-of-the-art laboratory infrastructure in the city of Durban.

The PIP is an extensive social, demographic, HIV and clinical research programme of an under-resourced rural population of 140,000 in an area of about 845 km^2^. Hlabisa is at the epicentre of the HIV epidemic in South Africa, where HIV prevalence among men and women aged 15–54 years in 2018 was 19% and 40% respectively [16]. It is situated in the most economically deprived district nationally; about 5% of adults have completed a higher education, 4% are covered by a medical aid scheme and unemployment rate is 62% [16]. AHRI has a memorandum of understanding with the DoH to support HIV care in the Hlabisa sub-district with ~ 30,000 PLHIV currently on ART (still in active care) in the 17 primary healthcare clinics (PHC) in the catchment area. This trial will be implemented in 10 of the 11 primary health care clinics that are located within the catchment area of the PIP.

The study involves collaboration of investigators from AHRI, the University of Sussex (UoS) and the University of Cape Town (UCT).

### Trial design

#### Gap analysis

We will use a retrospective chart review of HIV positive patients in care at the 10 trial clinics to identify the health systems gaps in VLM. We will create sampling frame of individuals who are in care and started ART 15–18 months previously and select a random sample of 800 individuals from this frame. Clinical notes of these individuals will be reviewed to identify any gaps in the VLM process, and to identify predictors of missing viral loads. This information will be used to develop a QIP that includes training of staff on the current South African ART guidelines, the importance of VLM and both health system and individual risk factors for suboptimal VLM.

#### Evaluation of the interventions

We will use an innovative effectiveness-implementation hybrid cluster-randomised trial in the 10 clinics to evaluate the effectiveness of the interventions for improving VLM and virological suppression compared with current care (Fig. 1). Clinics will be randomly allocated to either the intervention (QIP, viral load champion, and augmentation of TIER.Net) or current care.

**Fig. 1 Fig1:**
[figure not shown]
Trial design

### Participants

Gaps in VLM will be identified in HIV-positive patients aged ≥ 16 years who started ART in the previous 15–18 months in any of the 10 trial clinics through a retrospective review of their clinical charts.

The intervention will be evaluated in all patients aged ≥ 16 years who have been on ART for ≥ 12 months during the study’s baseline time period and attend any of the 10 trial clinics during a three-month recruitment period. No exclusion criteria will apply as there will be no individual enrolment to the trial, rather routine clinical data will be used for the evaluation of the outcomes.

### Description of the intervention

#### Quality improvement package

We will adapt the VL champion model described by Sunpath et al. [17]. This model identifies a VL champion in each clinic who dedicates 10 h per week to the role. The VL champion ensures those with high VL are appropriately managed with repeat VL tests including referral to a doctor for second line ART switch if required.

The prototype QIP will be adapted based on the identified clinical and process impediments in VLM from the gap analysis. All nursing/assistant staff in the intervention clinics will be trained on the QIP using the model by Sunpath et al. as described above [17]. Each intervention clinic will identify two key nurses who would act as VL champions. Their role will include tracing and recalling patients who need further assessments of their VL or switch to second-line regimen.

Training will be provided in the use of enhanced TIER.Net technology that will be developed as part of the trial and how to access reports on the dashboard system.

#### Augmentation of TIER.Net with a dashboard system

TIER.Net is an electronic database with varying levels of sophistication in both functionality and reports. It ranges from an off-line version of the electronic register to hybrid that is predominantly offline, with synchronisation centrally when bandwidth allows to a networked electronic version of the paper register [9]. The offline version of TIER.Net is in operation in the public ART programmes in which this study will be embedded.

As part of the proposed intervention, VL results will be imported into TIER.Net daily from the National Health Laboratory Service (NHLS) which will be linked to patients in TIER.Net based on multiple exclusive and linked deterministic rules using a combination of variables such as name, surname, sex, date of birth, date of visit, NHLS lab number, facility and folder number. The information contained in TIER.Net will be used to develop a dashboard which will display the following information:The proportion due VL tests as per South African ART guidelines.The proportion with high VLs (VL ≥ 50 copies/mL).The proportion lost to follow-up.Those with confirmed virological failure (repeat VL ≥ 1000 copies/mL after a first VL 1000 copies/mL measured ≥ 3 months apart).

A dashboard has the advantage of displaying a quick visual state of affairs and how this evolves with time. This will incorporate a text messaging functionality that can be used by healthcare workers/viral load champion to communicate with patients.

It is envisaged that these interventions will result in prompt identification of patients who require VLM, and improve clinical management of virological failure thereby improving the quality and efficiency of service delivery.

### Standard of care

Viral load results are manually captured on to the TIER.Net system with filing of the paper results in patients’ clinical notes for nurses’ review during routine appointments. This is used to produce a monthly enrolment and quarterly cohort reports for the central monitoring of the ART programme.

### Outcome measures

#### Health system gaps

Proportion of patients in survey sample with VL documented in clinical charts but not in TIER.NetProportion of patients with VL documented in TIER.Net but no results in clinical chartsProportion of patients with no VL in chart or TIER.Net (true missing VL = no assessment of VL undertaken)Predictors of true missing viral load (no record in either TIER.Net or clinical charts)

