#### Health system gap

The following data will be extracted from chart review into REDCap to document if (i) viral load was actually not measured as evidenced by a lack of documentation of this in the clinical charts and in TIER.Net (ii) there was documentation of a blood draw for VL and the date of the test (iii) results were filed and entered into the patient charts although not captured in TIER.Net (iv) there was evidence in patient chart that test was done but no results filed (v) VL results and date present in TIER.Net but not filed in patient charts.

All data collected from clinical chart reviews will be centrally stored in a master MONART database located at Africa Health Research Institute. This database will integrate data collected from clinical charts reviews, hospital information management system (HIS), ClinicLink and TIER.net. Database rules and constraints will be added and enforced on the master database to ensure that only valid data is stored in the database.

A study dashboard will be developed to assist the operational teams monitor the progress of the study.

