### Statistical analysis

#### Analysis of health system gaps

Analysis of data from the retrospective chart review of patients will quantify clinical and process impediments in VL testing system; results will inform the VL testing pathway, a QIP and required augmentation of TIER.Net. Proportions of patients with outcomes of interest will be tabulated; 95% confidence intervals will be calculated using clustered standard errors to take correlation within clinic into account. Factors associated with true missing viral load (not documented in TIER.Net or present in the patient chart) will be analysed using logistic regression with robust standard errors.

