The observed poor VLM in KwaZulu-Natal could be due to a number of reasons; patients may not have been aware of or empowered to request recommended blood tests, facility staff may be inadequately trained, or have insufficient time or resources to conduct blood tests when due, failure of results to reach clinics from the laboratory or failure to capture results on TIER.Net as these are manually entered [10]. The current study proposes to investigate the clinical and process impediments in VLM, including a review of patients’ clinical charts and comparing viral load in the charts with viral load data manually captured on TIER.Net in order to clarify whether the reported poor VLM was due to poor data entry in TIER.Net or actual failure to monitor viral loads. The proposed interventions will address all the steps potentially implicated in the poor management of VLM. This will involve training of staff on the current South African ART guidelines [26], designating a viral load champion who has administrative responsibility for identifying individuals due viral load tests or those with confirmed virological failure who need to be switched to second-line ART [17]. The automatic import of viral load results from the NHLS laboratories, also eliminates staffing challenges which contributes to backlogs in data capture and data entry errors. We also observed that amongst those with VLM who are experiencing virological failure, there is poor health system response to the clinical management of this situation. Only a minority of those with elevated viral load had a repeat viral load to confirm virological failure on ART, with only a small proportion of those with confirmed virological failure switching to second-line ART [10].

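### The gap survey equates having no VL in chart or TIER.Net with never having been assessed, although its own extraction items identify patients with a documented draw or test and no result

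*Protocol article*

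**What the plan says.** Three places in the Protocol article bear on this.

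- **Outcome measures, Health system gaps.** One outcome is the proportion with "no VL in chart or TIER.Net (true missing VL = no assessment of VL undertaken". The next is "Predictors of true missing viral load (no record in either TIER.Net or clinical charts".
- **Statistical analysis, Analysis of health system gaps.** The logistic regression is for "Factors associated with true missing viral load (not documented in TIER.Net or present in the patient chart".
- **Data collection, Health system gap.** The chart review extracts five items. Item (i) is that "viral load was actually not measured as evidenced by a lack of documentation of this in the clinical charts and in TIER.Net". Item (ii) is that "there was documentation of a blood draw for VL and the date of the test". Item (iv) is that "there was evidence in patient chart that test was done but no results filed". Items (iii) and (v) cover results found in one source but not the other.

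The Discussion says that comparing charts with TIER.Net should clarify "whether the reported poor VLM was due to poor data entry in TIER.Net or actual failure to monitor viral loads". It also lists results not reaching the clinic from the laboratory as one possible cause of poor monitoring.

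**The concern.** The outcome definition asserts an equality that the extraction form can show to be false. If the chart records a draw or a test but no result was filed and nothing reached TIER.Net, there is no VL in either source. The definition then labels that patient as never assessed, although the chart points the other way.

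Two different failures are merged: not testing, and not getting the result back. The survey's findings are to be used to adapt the quality improvement package, and its regression is meant to identify predictors of a missing VL. Merging the groups overstates failure to test, gives the lost-result group no outcome of its own, and can dilute predictors that act on only one of the two failures.

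**Working it through.** **1. Where each type of patient lands.**

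| Chart | TIER.Net | Gap outcome that applies |
|---|---|---|
| Result present | No VL | First outcome (in chart only) |
| No result | VL present | Second outcome (in TIER.Net only) |
| No draw, no test, no result | No VL | Third outcome, correctly labelled unassessed |
| Draw or test noted, no result (item ii or iv) | No VL | Third outcome, labelled unassessed |

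The last row is the problem. The first two outcomes each need a VL in one source, so this patient can enter only the third.

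**2. The article's own figures.** Inputs from Sample size justification, Health system gaps: n = 800, design effect (DE) 2 or 3, missing prevalence 30-60%, odds ratio (OR) 2.25, risk-factor prevalence 15-70% among those with non-missing VL.

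- Half-width = 1.96 × √(p(1−p) × DE / 800). At p = 30% this gives ±4.49 (DE 2) and ±5.50 (DE 3) points; at 60%, ±4.80 and ±5.88. The printed ±4.5, ±5.5, ±4.8 and ±5.9 reproduce.
- Power: effective n = 800 / 2 = 400, split by missing prevalence, normal approximation for two proportions, two-sided alpha 0.05 (assumed). The result is 86-98%, so the printed claim of more than 80% also reproduces.

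**3. Overstatement of never-tested.** Let s be the share of the labelled-missing group with a documented draw or test. The article does not give s; 10-40% is assumed. Overstatement = labelled prevalence × s.

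- 40% labelled missing: 0.40 × 0.10 = 4 points; 0.40 × 0.40 = 16 points.
- The overstatement equals the printed half-width at s = 4.5/30 = 15% to 5.5/30 = 18% when 30% are labelled missing, and at s = 4.8/60 = 8% to 5.9/60 = 10% when 60% are.

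**4. Dilution of a predictor.** Further assumption: the factor has OR 2.25 for never-tested and no association with a lost result. Let p0 be its prevalence among non-missing patients and p1 the prevalence implied by OR 2.25. In the merged group the prevalence is q = (1−s)p1 + s·p0, and the apparent OR is [q/(1−q)] / [p0/(1−p0)].

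Example: p0 = 0.15 gives p1 = 0.284. With s = 0.40, q = 0.6 × 0.284 + 0.4 × 0.15 = 0.2305, and the OR is about 1.70. Over p0 = 0.15 to 0.70:

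| s | Apparent OR |
|---|---|
| 10% | 2.03-2.10 |
| 25% | 1.77-1.90 |
| 40% | 1.56-1.70 |

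**5. Power on the corrected outcome.** Removing lost-result patients from the cases and placing them in the comparison group leaves fewer cases. At 30% labelled missing, the 120 effective cases become 90 (s = 25%) or 72 (s = 40%). For OR 2.25, power over the stated ranges is about 78-98% at s = 25% and 70-97% at s = 40%. On the merged outcome, under the dilution in step 4, it would be 59-84% and 40-67%.

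**The case against.** The strongest reply is that a chart note of a draw is itself a record. The predictor outcome speaks of a record, and item (i) refers to documentation of measurement rather than of a result. Read that way, true missing equals item (i) and nothing is merged. This is possible for the predictor line. It does not fit the proportion outcome, which turns on there being no VL, or the analysis section's "true missing viral load (not documented in TIER.Net or present in the patient chart", which refers to the viral load itself. At best the sections disagree and need reconciling.

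A second reply is that coding a derived variable is normally left to an analysis plan. That would answer an omission. Here a rule is stated, and a later plan would have to override it.

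Several limits do stand.

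- The share s and the null association with lost results are assumptions.
- Item (iv) is extracted and could be reported descriptively, so the information is not lost.
- A documented draw does not prove that an assay was run.
- Champions, training, automatic import and the dashboard are already specified, so a mislabelled proportion would not remove any of them.

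A reader might infer that the printed power claim is wrong. It is not: it concerns factors associated with missing VL as defined, and it reproduces.

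**Conclusion.** The point holds as an inconsistency between the gap outcome and its regression on one side and the extraction items on the other. As worded, a patient with a documented draw or test and no result in either source is classed as unassessed, on the very distinction the review is meant to clarify.

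How many patients this affects cannot be known from the article. The 4-16 point overstatement and the diluted odds ratios are illustrations. The first rests on 40% labelled missing and a 10-40% lost share; the second rests on the lost share and on a factor unrelated to lost results. The inconsistency itself depends on none of these.

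The reach is limited to the gap survey, its predictor model and the tailoring of the package. A reader might extend it to the trial result, but the randomised comparison and its primary outcome do not use this variable.

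**What to change.** In Outcome measures and in Analysis of health system gaps:

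1. Define true missing (never tested) as no result in chart or TIER.Net and no documented draw or test, that is, items (ii) and (iv) both negative, in line with item (i).
2. Add a gap outcome for a documented draw or test with no result in either source, worded so that a draw alone is not called a completed test.
3. Run the predictor regression on the corrected variable.

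The cost is a change of wording and one derived variable; the items are already in the planned extraction. The small downside is fewer cases, so more than 80% power for OR 2.25 is not assured in every scenario (about 78-98% at a 25% lost share, 70-97% at 40%). A draw that left no trace in the chart would still go undetected.
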